# Resistance training and clinical status in patients with postdischarge symptoms after COVID-19: protocol for a randomized controlled crossover trial “The EXER-COVID Crossover Study”

**DOI:** 10.1186/s13063-022-06608-y

**Published:** 2022-08-09

**Keywords:** COVID-19, Multicomponent exercise, Inflammation, Immunology

## Abstract

**Background:**

Physical exercise induces a coordinated response of multiple organ systems, including the immune system. In fact, it has been proposed that physical exercise may modulate the immune system. However, the potential effect of an exercise program on COVID-19 survivors has not been investigated. Thus, the aim of this study is to evaluate the modifications in immunological parameters, physical condition, inflammatory profile, and perceived persistent symptoms after 6 weeks of supervised resistance training (RT), in addition to the standard care on the clinical status of patients with persistent COVID-19 symptoms. The objective of this protocol is to describe the scientific rationale in detail and to provide information about the study procedures.

**Methods/design:**

A total of 100 patients with postdischarge symptoms after COVID-19 will be randomly allocated into either a group receiving standard care (control group) or a group performing a multicomponent exercise program two times a week over a period of 6 weeks. The main hypothesis is that a 6-week multicomponent exercise program (EXER-COVID Crossover Study) will improve the immunological and inflammatory profile, physical condition, and persistent perceived symptoms (fatigue/tiredness, musculoskeletal pain, and shortness of breath) in patients with postdischarge symptoms after COVID-19.

**Discussion:**

Our results will provide insights into the effects of a multicomponent exercise program on immunological parameters, physical condition, inflammatory profile, and persistent perceived symptoms in patients with postdischarge symptoms after COVID-19. Information obtained by this study will inform future guidelines on the exercise training rehabilitation of patients with postdischarge symptoms after COVID-19.

**Trial registration:**

NCT04797871, Version 2. Registered on March 15, 2021.

**Supplementary Information:**

The online version contains supplementary material available at 10.1186/s13063-022-06608-y.

## Background and rationale

In 2019, a new coronavirus was identified from an outbreak originating in the city of Wuhan, China. At present, this virus is known as severe acute respiratory syndrome coronavirus 2 (SARS-CoV-2), and the resulting disease is known as coronavirus disease 2019 (COVID-19). On January 30, 2020, the World Health Organization (WHO) declared this disease a public health emergency of international scope, and in less than 2 months, on March 11, it was classified as a pandemic [1]. The clinical picture associated with this virus is referred to as COVID-19. In cases of COVID-19, the SARS-CoV-2 virus promotes an inflammatory response in the lung parenchyma that is characteristic of the pathology of SARS and is mediated by the cytokine interleukin-1β (IL), which is activated by the inflammasome complex IL-6 and tumoral necrosis factor-alpha (TNF).

A characteristic of the condition produced by this pathogen is that when symptoms appear, the condition can worsen very quickly, although virulence is related to pathogen/host symbiosis. The primary symptoms are fever (80%), nonproductive cough (56%), fatigue (22%), and myalgia (7%), and these may coexist with symptoms related to a possible neurotropism, such as anosmia or headache [2]. Other symptoms may include dyspnea, chills, odynophagia, headache, angina, or conjunctivitis [3]. Although COVID-19 symptoms can be mild or moderate for most people, the disease can lead to serious medical complications and, in some cases, death [3]. Additionally, older adults and people with chronic noncommunicable comorbidities, such as diseases of the cardio-cerebro-circulatory system, certain types of cancer and pulmonary, metabolic, and/or renal diseases, have a higher risk of becoming ill with COVID-19 and developing serious complications.

Because COVID-19 is a new disease, much of its clinical course remains uncertain, particularly the possible long-term health consequences, if any [4]. For example, it is estimated that approximately 20 million people worldwide have completely recovered from COVID-19; however, patients with persistent severe symptoms and even substantial target organ dysfunction have been reported after SARS-CoV-2 infection [5]. Along this line, the COVID-19 Symptomatology Study reports that 1 in 10 patients diagnosed with SARS-CoV-2 remain symptomatic beyond 3 weeks, and some of them have persistent symptoms 6 months after the acute picture [6]. Although there is no consensus definition of chronic or persistent COVID-19 (understood as symptoms that extend beyond 12 weeks), it has been reported that COVID-19 survivors frequently report symptoms such as chronic fatigue, dyspnea on minimal exertion, joint pain, and/or chest pain [7]. In addition to these symptoms, coexisting dysfunction of specific tissues, such as the heart, lung, and brain, has been reported [8].

Although the etiopathogenesis of the symptomatology in patients with chronic COVID-19 is not clear, it has been hypothesized that these complications could be the consequence of direct tissue invasion by the SARS-CoV-2virus, possibly mediated by (*i*) the presence of angiotensin-converting enzyme receptor 2 (ACE-2), (*ii*) the exacerbated inflammatory response (also called cytokine storm), which is associated with damage to the immune system, or (*iii*) the state of hypercoagulability described in severe COVID-19.

In terms of persistent symptoms (for example, pain and/or chronic fatigue), several studies have described a relationship between the activation of the cannabinoid system and regular physical exercise (especially at high training intensities), which would partially explain effects of exercise on improving mood, pain perception, and fatigue in humans [9, 10]. In animal studies, authors of [11, 12] have described the analgesic activity resulting from the regulation of activation of the endocannabinoid system, and authors such as Crombie et al. [13] reported that a single session of moderate- to vigorous-intensity physical exercise was sufficient to induce analgesia through endocannabinoids and described the effect of such activity on the CB1 and CB2 receptors at the peripheral, medullary, and supramedullary levels in rats, suggesting plausible molecular mechanisms that could be applied to patients with chronic pain and/or fatigue conditions, such as those reported in patients with COVID-19. The excessive consumption of alcohol also increases the risk of contracting diseases associated with severe manifestations of COVID-19 [14], not because of deterioration in the physiological function of target organs and general immune function but also because of the negative effects of the COVID-19 pandemic on health and social behavior. Overweight and obesity are among the most common comorbidities in patients hospitalized with COVID-19, in part due to the low-grade subclinical inflammation associated with excess weight/adiposity, which deteriorates the immune response to viral infection, and/or to the close relationship between type 2 diabetes and a state of oxidative stress that limits cardiovascular and respiratory function [15]. In addition, physical inactivity can indirectly influence the progression and complications of COVID-19 [16]. This is because physical inactivity is associated with obesity/overweight, and metabolic risk factors are associated with a severe picture of COVID-19. Consequently, it is important to maintain a healthy lifestyle, especially the practice of physical exercise.

### Exercise can improve clinical status in patients with postdischarge symptoms after COVID-19

There is irrefutable evidence of the beneficial role of physical exercise in the prevention of disease, as a complementary treatment for chronic diseases and in promoting psychological well-being [16–18]. In addition to promoting optimal physical and mental health, an active and healthy lifestyle throughout the lifespan strengthens and improves immune function and even reduces the risk of viral and/or chronic degenerative diseases [17]. Exercise may have a protective effect on the immune system, whose optimal state is crucial to an appropriate response to the threat of COVID-19 [18].

The mechanisms by which physical activity influences the immune system have been little elucidated and are currently a subject of debate, but it is possible to affirm certain physiological and psychological perceptions, which are described as follows: Physical exercise, when practiced regularly, increases the subject’s immune competence (that is, the ability of lymphoid cells to produce a humoral or cellular immune response when stimulated by an antigen) [19]. This benefit seems to be accentuated among older adults, reducing their immunosenescence and delaying immune aging [20]. This increase in immune competence occurs through increased concentrations of CD4+ cells, which are responsible for detecting pathogens and activating the immune response [21].

Physical exercise, through different mechanisms related to the sympathetic, humoral, and hormonal response, favors the release of myokines from skeletal muscle, which can help maintain immune competence. It has been shown that muscle-derived interleukin- (IL-) 6 directs immune cell trafficking to areas of infection, while IL-7 can stimulate the production of thymus T cells, and IL-15 helps maintain T cell and natural killer (NK) cell homeostasis in the periphery. Some myokines also have antiproliferative effects that can induce apoptosis (programmed cell death) in solid tumor cells. All these cells work together to increase immune defense [22].

Physically active people show better control of latent viral infections, even during periods of stress such as isolation and confinement, events that can inhibit many critical functions of the immune system through the increase in glucocorticoids (for example, cortisol) [23]. Therefore, the ability of physical activity to mitigate the harmful effects of stress on immunity is highlighted. Physical activity seems to strengthen the immune response of the mucous membranes by increasing the concentration of immunoglobulin IgA, which could be beneficial for preventing some types of infections, particularly respiratory infections such as COVID-19 [24]. In older adults, an amplification of the T helper 1 (TH1) lymphocyte pattern without changes to TH2 has been described. That is, regular physical activity increases the number of T lymphocytes, B cells, and NK cells and increases the production of interferon gamma and IL-6 [25]. It has also been reported that physical activity can stimulate immune function and reduce inflammation and has several physiological and psychological benefits, such as the reduction of stress and anxiety [26]. Exercise also significantly increases antibody levels after vaccination, especially in older adults; therefore, the results of advances in this field should focus primarily on vulnerable people, such as health professionals, elderly adults and patients with neoplasms, chronic diseases, and immunosuppression [27].

### Clinical outcomes responses to resistance training are unknown in patients with postdischarge symptoms after COVID-19

Resistance training (RT) has modulating effects in humans, a finding that is of great importance for the immune system’s response to various infectious agents in cardiovascular degenerative conditions and in cases of chronic immunodeficiency [28–30]. It has been reported that the effect of RT changes according to its intensity, the presence of chronic immunodeficiency and age [31–33]. In addition, RT, but not intense exercise, has a protective effect [34–36]. Markers of endothelial inflammation and stress and lymphocyte subpopulation (LSP) change with RT, according to the current literature [28, 37]. This effect has been described in humans who engage in acute exercise at different intensities, but the effect of chronic RT on COVID-19 survivors has not been determined.

Considering that in postdischarge symptoms after COVID-19 population, the exercises that are achieved may be psychologically demanding, due to heightened cardiovascular and neuromotor effort, it is surprising that an examination of clinical status outcomes in RT for the post-COVID-19 syndrome population is not currently available. An understanding of cardiovascular and immunological parameters of response to exercise, like psychosocial outcomes, and how RT may affect such outcomes, would provide important information about the potential sustainability of exercise and its applicability in post-COVID-19 syndrome rehabilitation. To the best of our knowledge, we proposed a first clinical trial of randomized controlled crossover design using international recommendations with an emphasis on twice-a-week strength training, in patients with persistent COVID-19 symptoms [38].

### Objectives

The primary objective of this study is to compare the effects of 6 weeks of RT vs. standard care on the clinical status of patients with persistent COVID-19 symptoms. Changes in clinical status will be determined by examining changes in perceived persistent symptoms (i.e., fatigue/tiredness, musculoskeletal pain, shortness of breath). In addition, the secondary objective of this study is to compare the effects of RT on measures of immunological and inflammatory markers, cardiovascular health, and psychosocial responses to exercise. Changes in immunological and inflammatory markers will be measured by assessing lymphocyte immunophenotypes and cytokine assays. Changes in cardiovascular health will be measured by assessing resting blood pressure, arterial stiffness, heart rate variability, maximal aerobic capacity (V̇O_2_max), muscle strength, and body composition. Psychosocial responses to exercise will examine the effect of RT on perceived persistent symptoms (i.e., fatigue/tiredness, musculoskeletal pain, shortness of breath) in response to the exercise intervention. The RT exercise intervention will be conducted using a whole-body paradigm, which will utilize Smart Strength machines (eGym® GmbH, München, Germany) and cycle ergometer.

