### Research hypothesis

We hypothesize that RT will be more effective than standard care in improving clinical health status. The main hypothesis is that by applying a supervised RT (EXER-COVID Crossover Study) for 6 weeks, we could reduce the perception of persistent symptoms. We could increase physical performance (V̇O_2_max and/or muscle fitness) through the effects of mechanical and endocrine action, and we could modulate the production of immunological and inflammatory markers due to skeletal muscle contraction, which could contribute to reducing the inflammatory process that is usually established in COVID-19 infection. Exercise training is also expected to be more effective in improving cardiovascular measures of resting blood pressure, arterial stiffness, and heart rate variability as compared to no training. If successful, our trial would provide evidence that exercise training has potential for patients with postdischarge symptoms after COVID-19.

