### Primary outcome

The primary outcome is the change in aerobic exercise capacity measured by (V̇O_2_max) before and after the intervention period. Graded exercise tests will be performed on a bicycle ergometer (Lode B.V., Groningen, The Netherlands) to determine the maximal oxygen uptake. The test will start with a 3-min warm-up at 25 W. Warm-up will be immediately followed by a 25-W increase every 2 min until exhaustion, which is categorized as voluntary exhaustion or failure to maintain rounds per minute above 60. Breath-by-breath gas exchange data will be collected using a metabolic gas analyzer (QUARK, Cosmed, Rome, Italy) and used to determine V̇O_2_max and total energy expenditure during exercise. The staggered phase will have a maximum duration of 8 to 12 min, and the cadence of the pedal will not be altered during the effort (approx. 1.23 Hz or 50–60 RPM). The heart rate (HR) will be measured with a cardiotachometer (Polar Vantage NV, Finland) every 5 s.

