### Secondary outcomes

#### Long-term COVID manifestations

Data on specific symptoms potentially correlated with long-term COVID-19 will be obtained using a standardized questionnaire administered at enrollment via PROMs [40]. At baseline and at the end of each crossover period, participants will be asked about the presence or absence of symptoms related to long-term COVID-19 and whether each symptom persisted at the time of the visit. More than 1 symptom could be reported that reflects symptoms such as functional limitations and clinical characteristics (i.e., nausea/vomiting, impaired visual acuity or blurry vision, anosmia, dizziness, depression, chills, weakness, musculoskeletal pain, palpitations/tachycardia, change of appetite, frustration, cognitive involvement, anxiety/irritability, dryness, impaired concentration, and headache).

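### The stated primary objective and main hypothesis concern symptoms, but the only primary outcome, and the sample size, concern VO2max

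*Protocol article*

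**What the plan says.** The Objectives section of the protocol article sets the primary objective as follows: "compare the effects of 6 weeks of RT vs. standard care on the clinical status of patients with persistent COVID-19 symptoms". It then defines clinical status: "Changes in clinical status will be determined by examining changes in perceived persistent symptoms (i.e., fatigue/tiredness, musculoskeletal pain, shortness of breath". VO2max appears later in the same section, within the secondary objective: "Changes in cardiovascular health will be measured by assessing resting blood pressure, arterial stiffness, heart rate variability, maximal aerobic capacity". That section also lists the same three symptoms a second time, under the secondary objective, as psychosocial responses.

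The Research hypothesis section states as its main hypothesis that with supervised training "we could reduce the perception of persistent symptoms"; gains in VO2max and muscle fitness come in the next sentence. The abstract words the main hypothesis more broadly, saying that the programme "will improve the immunological and inflammatory profile, physical condition, and persistent perceived symptoms (fatigue/tiredness, musculoskeletal pain, and shortness of breath".

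The Primary outcome section reads: "The primary outcome is the change in aerobic exercise capacity measured by" VO2max. The Sample size section is built on a 1-MET difference in cardiorespiratory fitness. Symptoms sit under Secondary outcomes: "At baseline and at the end of each crossover period, participants will be asked about the presence or absence of symptoms related to long-term COVID-19". The printed symptom list there ends: "weakness, musculoskeletal pain, palpitations/tachycardia, change of appetite, frustration, cognitive involvement, anxiety/irritability, dryness, impaired concentration, and headache".

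The section on analysis methods and missing data attaches the 0.05 level to the primary analysis without naming the endpoint.

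**The concern.** A primary outcome should be the measurement that answers the primary objective. Here the order is reversed between sections. What the Objectives rank first (symptoms) is measured as a secondary outcome, and what they rank second (VO2max, as part of cardiovascular health) is the primary outcome and drives the sample size.

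Two things are at stake. First, a significant VO2max result could be reported as confirming the main hypothesis although it says nothing directly about fatigue, pain or breathlessness. Second, with two competing claims to be primary, a reader of the final report cannot tell from this article alone which result was meant to carry the confirmatory conclusion.

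The symptom outcome also fits its objective poorly as printed. Two of the three symptoms that define clinical status are absent from the list, and the recording is described as presence or absence, whereas the Discussion speaks of lowering the degree to which symptoms are perceived.

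**Working it through.** **1. Which endpoint each section ranks first**

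| Section | Symptoms | VO2max |
|---|---|---|
| Objectives | primary (and listed again under secondary) | secondary, within cardiovascular health |
| Research hypothesis | main hypothesis | follows in the next sentence |
| Abstract, main hypothesis | one of several domains | covered by physical condition |
| Primary and Secondary outcomes | secondary | primary |
| Sample size | only a general remark on patient-reported outcomes | basis of the calculation |
| Discussion, primary purpose | not named | covered by physical condition |

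The Objectives and Research hypothesis sections point one way, the outcome and sample-size sections the other. The abstract and Discussion do not settle it.

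**2. Symptom items against the objective.** The list under Long-term COVID manifestations has 16 entries. Musculoskeletal pain is there. Fatigue/tiredness is not (weakness is the nearest entry), and neither is shortness of breath. That is one of three. No other outcome section names a fatigue or breathlessness measure.

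**3. What the sample size rests on.** Inputs from the Sample size section: difference 3.5 mL/kg/min, SD 5.4 (printed with a percent sign; read here as mL/kg/min, an assumption), two-sided 0.05, 80% power, 42 per group.

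- n per group = 2 × (1.960 + 0.842)² × (5.4/3.5)² = 37.4, so 38 per group and 76 in total. The plan states 84.
- Power at 42 per group = Φ(3.5/(5.4 × √(2/42)) − 1.960) = Φ(1.010) = 84.4%.
- Taking the SD literally as 5.4% of an assumed VO2max of 20 to 40 gives only 2 to 6 per group.

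The printed 84 is not reproduced exactly and errs on the conservative side. That is a separate matter. What counts here is that the calculation concerns VO2max and nothing else.

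**4. What the symptoms get.** The only statement is that power suffices for patient-reported outcomes at a Cohen's d of 0.6 or more.

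- Parallel comparison, 42 per group, d = 0.6, two-sided 0.05: Φ(0.6/√(2/42) − 1.960) = Φ(0.790) = 78.5%.
- The same with 0.05 split over three symptoms (0.0167 each): Φ(2.750 − 2.394) = 63.9%.
- A yes/no symptom, McNemar test on 84 pairs: power = Φ((δ√n − 1.960√π)/√(π − δ²)), where π is the sum and δ the difference of the two discordant rates. Rates of 20% and 10% give 38.5%; 30% and 10% give 83.9%.

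The discordant rates are assumptions, since the article gives no symptom rate. They show that power for a yes/no symptom is undetermined, not that it is inadequate.

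**5. If either endpoint could be presented as primary.** With two tests at 0.05 and independence: 1 − 0.95² = 9.75%. Positive correlation between fitness and symptoms would lower this.

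**The case against.** The strongest reply is that the operative parts of the article agree. One outcome is labelled primary, the trial is sized on that outcome, and symptoms are listed as secondary. On that reading the 0.05 for the primary analysis plainly belongs to VO2max, and the Objectives are merely loosely worded. The abstract's main hypothesis includes physical condition, which VO2max addresses.

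Most of this stands, and it limits the point in four ways.

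- A reader might infer that the trial cannot answer its main question. The documents do not support that. Symptoms are collected at baseline and after each period, with McNemar and two-proportion tests planned. The answer would come from a secondary outcome, so it is less confirmatory but not absent.
- A reader might infer that fatigue and breathlessness go unmeasured. The questionnaire is cited but not shown, and the Objectives state twice that these symptoms will be examined. The list's completeness is unclear: its lead-in is illustrative, but the items follow *i.e.* Only the omission from the printed list is established.
- A reader might infer that changes in severity cannot be detected. The symptom list is described as presence or absence, but the scoring of the full instrument is not shown, and a Cohen's d for patient-reported outcomes implies that some are continuous.
- A reader might count the domains in the abstract's hypothesis and compute a larger error rate. No domain there is given its own primary test, so no such figure follows. Even the 9.75% requires setting aside the single primary label.

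The reply does not remove the contradiction. The Objectives class VO2max as secondary in so many words, and no later passage says that the outcome section overrides them. A separate analysis plan may order the testing, but it cannot make this article's primary objective and primary outcome the same thing.

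**Conclusion.** The point holds. The stated primary objective and the main hypothesis in the body of the article concern three perceived symptoms. The only primary outcome and the sample size concern VO2max, which the Objectives place under the secondary objective. The powered test therefore leaves the stated primary objective to a secondary presence-or-absence outcome, whose printed list names one of the three defining symptoms.

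The consequence is mainly for interpretation: a positive VO2max result would not by itself confirm symptom benefit. The 9.75% is an illustrative ceiling under independence and applies only if either endpoint could be headlined as primary; it is not the plan's error rate. Whether fatigue/tiredness and shortness of breath are collected cannot be decided from the article. The mismatch between sections rests on the text alone and needs no numerical assumption.

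**What to change.** Before the analysis begins:

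1. Restate the primary objective and main hypothesis as the effect on VO2max, in the abstract, Objectives, Research hypothesis and Discussion, to match the primary outcome and sample size. State that the 0.05 in the analysis section applies to the VO2max comparison.
2. Present the three named symptoms as secondary and remove their double listing in the Objectives. Preferably make them the first key secondary, tested only if VO2max is significant. The analysis plan can carry the detail.
3. Correct the printed symptom list. If the questionnaire collects fatigue/tiredness and shortness of breath, add them to the list. If it does not, add them for the remaining visits and state that earlier participants lack baseline values.

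Steps 1 and 2 cost only wording and a dated amendment. Step 3 costs wording if the items exist. If they do not, it recovers little: recruitment began in March 2021 and was expected to end by September 2022, and the article appeared in August 2022, so most participants would probably have no baseline value for a new item.

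Naming a symptom measure as primary would also remove the contradiction, but it would need a defined measure and a new power calculation. With recruitment nearly complete, aligning on VO2max is the practical choice.
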